# Cost-Effectiveness of perioperative Vaginally Administered estrogen in postmenopausal women undergoing prolapse surgery (EVA trial): study protocol for a multicenter double-blind randomized placebo-controlled trial

**DOI:** 10.1186/s12905-021-01587-9

**Published:** 2021-12-31

**Keywords:** Pelvic organ prolapse, Vaginal estrogen therapy, Postmenopausal, Wound healing, Pelvic reconstructive surgery, Recurrence, Cost-effectiveness

## Abstract

**Background:**

Surgery for pelvic organ prolapse (POP) is associated with high recurrence rates. The costs associated with the treatment of recurrent POP are huge, and the burden from women who encounter recurrent POP, negatively impacts their quality of life. Estrogen therapy might improve surgical outcome for POP due to its potential beneficial effects. It is thought that vaginal estrogen therapy improves healing and long-term maintenance of connective tissue integrity. Hence, this study aims to evaluate the cost-effectiveness of perioperative vaginal estrogen therapy in postmenopausal women undergoing POP surgery.

**Methods:**

The EVA trial is a multi-center double-blind randomized placebo-controlled trial conducted in the Netherlands comparing the effectiveness and costs-effectiveness of vaginal estrogen therapy. This will be studied in 300 postmenopausal women undergoing primary POP surgery, with a POP-Q stage of ≥ 2. After randomization, participants administer vaginal estrogen cream or placebo cream from 4 to 6 weeks preoperative until 12 months postoperative. The primary outcome is subjective improvement of POP symptoms at 1 year follow-up, measured with the Patient Global Impression of Improvement (PGI-I) scale. Secondary outcomes are POP-Q anatomy in all compartments, re-interventions, surgery related complications, general and disease specific quality of life, sexual function, signs and complaints of vaginal atrophy, vaginal pH, adverse events, costs, and adherence to treatment. Follow up is scheduled at 6 weeks, 6 months and 12 months postoperative. Data will be collected using validated questionnaires and out-patient visits including gynecological examination performed by an independent gynecologist.

**Discussion:**

This study investigates whether perioperative vaginal estrogen will be cost-effective in the surgical treatment of POP in postmenopausal women. It is hypothesized that estrogen therapy will show a reduction in recurrent POP symptoms and a reduction in reoperations for POP, with subsequent improved quality of life among women and cost savings.

*Trial registration*Netherlands Trial Registry: NL6853; registered 19-02-2018, https://www.trialregister.nl/trial/6853. EudraCT: 2017-003144-21; registered: 24-07-2017.

**Supplementary Information:**

The online version contains supplementary material available at 10.1186/s12905-021-01587-9.

## Background

Pelvic organ prolapse (POP) is a common disorder, where 38–50% of postmenopausal women are affected with Stage II prolapse or more [1–4]. Women with POP can experience a sensation of heaviness or bulging in the vagina, and can have problems with voiding, defecation and sexual functioning. These POP-related symptoms adversely affect women’s quality of life, body image as well as their productivity [5–7].

Surgery is often indicated to relieve symptoms, and women have a 11–19% lifetime risk of undergoing surgery for POP [8–10]. However, surgery for POP is associated with high recurrence rates around 30% [9, 11–14], which necessitates additional research to improve surgical outcome for POP.

It is hypothesized that vaginal estrogen therapy might improve surgical outcome for POP and subsequent POP-related symptoms. Yet estrogen therapy has shown to be beneficial for women with divers pelvic floor pathology. Vaginal atrophy can be solved by the use of vaginal estrogen therapy, effectively treating bothersome symptoms like vaginal dryness, and itching of the vulva [15]. In addition, a reduction of symptoms has also been described in women with prolapse symptoms, stress urinary incontinence, overactive bladder symptoms and recurrent cystitis, after using vaginal estrogen [16–18]. The hypothesis is that estrogen results in a thickening of the vaginal wall and urothelium, and improves vascularization of the pelvic floor [18]. Multiple in-depth studies have been performed to investigate the potential beneficial effects of vaginal estrogen therapy [19–21]. A randomized trial showed that the use of vaginal estrogen prior to prolapse surgery increased the production of collagen and reduced degradative enzyme activity [22]. Moreover, estrogens act on the cutaneous wound healing response by modulating the inflammatory response, cytokine expression and matrix deposition [18]. In addition, estrogens accelerate re-epithelialization, stimulating angiogenesis and wound contraction, and regulate proteolysis [18, 23]. Consequently, it is thought that women with low estrogen levels who undergo surgery for POP might have a higher risk of recurrence of their POP—and subsequent symptoms—due to poor vascularization and a thin vaginal wall, compromising their healing capacity. Vaginal estrogen administration is expected to improve healing and long-term maintenance of connective tissue integrity of the pelvic floor [23, 24] and therefore reduce risk of recurrence. Nevertheless, limited supportive data can be found regarding the use of perioperative estrogen to improve clinical outcomes following surgical intervention for prolapse. This was confirmed in a Cochrane review which concluded that a randomized controlled trial is needed to assess perioperative estrogen therapy as adjunctive treatment for women undergoing prolapse surgery [25, 26]. Hence, this study is conducted and aims to evaluate the cost-effectiveness of perioperative vaginal estrogen therapy in postmenopausal women undergoing POP surgery. The results of this study will provide evidence whether the use of estrogen is effective in reducing recurrent POP symptoms, reoperations for POP and hence its cost-effectiveness.

## Methods

### Study design and setting

The EVA trial is a multicenter, double-blind randomized placebo controlled clinical trial. Postmenopausal women undergoing primary POP surgery with a POP-Q stage of ≥ 2, are eligible for the study and will be asked for informed consent to participate. After enrollment, participants are randomized and administer either vaginal estriol or placebo from 4 to 6 weeks before POP surgery till 12 months postoperative.

Recruitment will take place in a multicenter setting in 22 participating centers in the Netherlands, i.e. university, teaching and non-teaching hospitals. A list of current study sites can be obtained via the website [27]. Gynecologists and residents, supported by research nurses, will counsel women, ask informed consent, perform randomization and collect data. Both participants and investigators will be blinded for allocation. The study design is presented in Fig. 1. The study is conducted in cooperation with the urogynecology consortium of the Netherlands and the Dutch NVOG Consortium 2.0 (Dutch Consortium for Healthcare Evaluation and Research in Obstetrics and Gynecology).

**Fig. 1 Fig1:**
[figure not shown]
Study design: schedule of enrolment, interventions and assessments. *EQ-5D-5L* emotional quotient, 5 dimensions, 5 levels, *iMCQ* Medical Consumption Questionnaire, *iPCQ* Productivity Cost Questionnaire, *PFDI-20* Pelvic Floor Disability Index-20, *PFIQ-7* Pelvic Floor Impact Questionnaire-7, *PGI-I* Patient Global Impression of Improvement, *PISQ-IR* Pelvic organ prolapse Incontinence Sexual Questionnaire-IR, *POP* Pelvic Organ Prolapse, *POP-Q* Pelvic Organ Prolapse Quantification

### Participants and eligibility criteria

#### Inclusion criteria

Postmenopausal women (> 1 year amenorrhea)Pelvic organ prolapse; POP-Q stage ≥ 2 [28]Women that will undergo primary POP surgery with native tissue repair, including at least anterior OR posterior vaginal wall repair

#### Exclusion criteria

Previous POP surgery in concerning compartment;Prolapse repair using meshCurrent vaginal infectionUse of estrogens in the past 12 monthsContraindications for topical estrogenKnown, past or suspected estrogen-dependent malignant tumorsInsufficient knowledge or understanding of the Dutch language

### Interventions

After obtaining informed consent, eligible women will be assigned to either estriol cream (Synapause-E3; 1 mg/g) or placebo cream. Both creams are vaginally administered, ante noctem and come with a special applicator. The applicator allows the participant to insert the correct amount of cream deep into the vagina. Therefore, the participant lies on her back with slightly bent, spread legs. The cream-filled applicator is applied deep into the vagina. Then the applicator will be emptied and removed from the vagina. During the first 2 weeks of use, 0.5 g cream will be used once a day. Thereafter, 0.5 g cream will be used vaginally twice per week. The first 2 weeks postoperative, no cream will be used. The total duration of this intervention will be 58 weeks; 6 weeks prior to POP surgery (with a minimum of 4 weeks) and 52 weeks after POP surgery. This dosage schedule corresponds with the standard dosage schedule used in clinical practice. Women will receive routine clinical care and remain blinded to treatment allocation until the primary analysis has been completed.

Preparation and labelling of study medication will be done according to Good Manufacturing Practice guidelines. Manufacturing and packaging of both estriol vaginal cream (1 mg/g) and placebo cream is performed by Aspen Pharmacare. During the manufacturing process of estriol vaginal cream and placebo cream, the exact same ingredients were used, except from estriol. The active product ingredient estriol is no component in the placebo cream. Labelling is performed by the pharmacy of the Academic Medical Center Amsterdam.

#### Low-dose vaginal estrogen

The low-dose vaginal estrogen used in this study is preferred over systemic (oral) estrogens, because systemic use is associated with an increased risk of thrombosis and endometrial, breast and ovarian cancer. Low-dose regimens are also preferred over intermediate- or high dose methods since absorption and systemic effects occur with high-dose vaginal estrogen preparations [29–34]. Although vaginally administered low-dose estrogen could result in a minimal systemic uptake, serum estrogen levels remain within the normal range for postmenopausal women and no endometrial or myometrial effects are seen [22, 35–40]. Therefore, vaginal estrogens are an effective and safe strategy and is in line with the global consensus statement on menopausal hormonal therapy, where low-dose estrogen is preferred [41].

### Outcome measures

The primary outcome is subjective improvement of POP symptoms at 1 year follow-up; the percentage of women with much or very much improvement of POP symptoms, measured with the Patient Global Impression of Improvement (PGI-I) scale [42]. PGI-I is a 7-point Likert scale, with scores ranging from very much worse to very much improved. Success is defined as ‘much or very much’ improvement.

Secondary outcomes are surgical success, POP-Q anatomy in all compartments, surgery related complications, general quality of life, disease specific quality of life (micturition and defecation), sexual function, signs and complaints of vaginal atrophy, vaginal pH, adverse events, costs, and adherence to treatment. Surgical success is defined as the absence of POP beyond the hymen (POP-Q at gynecological examination), the absence of bulge symptoms (absence of bulge symptoms is defined as a negative response to the question, “Do you see or feel a bulge in the vaginal area”), and absence of reoperation or additional pessary therapy for POP [43]. Follow up is scheduled at 6 weeks, 6 months and 12 months postoperative. Data will be collected using validated questionnaires (See also ‘Data collection’ and Fig. 1) and out-patient visits including gynecological examination are performed by an independent gynecologist.

### Patient recruitment and consent

Eligible women receive oral and written information on study participation during a regular hospital visit for POP complaints. Women will be contacted by telephone for further information by the gynecologist, resident or research nurse. Women will be given sufficient time to read the patient information and the informed consent form and get the opportunity to ask questions. If a woman agrees to participate in the study, written informed consent will be obtained and countersigned by the investigator where after randomization will be performed, according to Good Clinical Practice (GCP).

### Randomization

Women will be randomized in a 1:1 ratio to perioperative treatment with estriol or perioperative treatment with placebo using computer-generated randomly permuted blocks of sizes 4, 6 and 8. Blinded randomization will be performed by the participating center using online software (Castor Electronic Data Capture, Amsterdam, the Netherlands [online] available at: http://castoredc.com). The central coordinating pharmacy of the Academic Medical Center Amsterdam receives an automatically generated email containing the allocated treatment for each randomized patient from the Castor system. After also receiving a doctor’s prescription, the pharmacy will deliver study medication at the participant’s home address by courier service.

### Blinding

Study medication will be blinded. Both estriol cream and placebo cream are provided to the participant in identical blank white tubes, marked with a study label. All physicians, researchers, research nurses, outcome assessors and participants will remain blinded to treatment allocation until the primary analysis has been completed. During the conduct of the study, only the pharmacy of the Academic Medical Center Amsterdam will have access to the blinding information of the study. With the approval of the principal investigator, a local investigator could decide to reveal a participant’s allocation for urgent medical reasons only. Unblinding will be performed by the central coordinating pharmacy at the Academic Medical Center Amsterdam.

### Data collection

All data will be systematically recorded by trained research nurses or gynecologists in an electronic Case Report Form in web-based data management software: Castor EDC. Castor EDC allows researchers to collect and manage data in accordance with the GCP guidelines [44]. To improve data quality, range checks are incorporated in the electronic Case Report Form. The software will randomly assign an unique numeric code for every subject that bears no relation to initials or date of birth. Data handling will be done with coded data, with the key (code to personal information linkage) only available to the local investigator and the research nurse working in the participating center. Persons who have access to the coded data include: investigators, research staff, monitoring and quality assurance personal. Data will be preserved for the duration of 15 years. The handling of personal data complies with the European General Data Protection Regulation. Participants will be followed from baseline (pre-operatively) up to 1 year after POP surgery. During the follow up period the following data will be collected:

#### Hospital visits

The participant will visit the hospital prior to starting with the study medication, 6 weeks postoperative and 12 months postoperative. History and gynecological examination including POP-Q, vaginal pH and assessment of vaginal atrophy will be performed. To reduce interviewer bias, the POP-Q measurement at 12 months postoperative will be done by an independent examiner—instead of the surgeon. Unscheduled visits and phone calls are also recorded in respect to additional costs.

#### Surgery and postoperative data

Surgery time, blood loss, surgery related complications (including excessive blood loss, hematoma, lesion of the gut, bladder, ureter or urethra, urinary retention, urinary tract infection, and prolonged hospitalization) are recorded.

#### Questionnaires and diary

Participants will be asked to complete online questionnaires, generated in Castor EDC (when preferred, it is possible to complete the questionnaires on paper). Participants will receive 2 or more of the following questionnaires at baseline and 6 weeks, 6 months and 12 months postoperative (See also Fig. 1):Questionnaire on baseline characteristics and medical history (including age, length, weight, parity, education, history of diabetes, respiratory diseases and smoking, family history of POP).Patient Global Impression of Improvement (PGI-I): to assess subjective improvement of POP symptoms [42].EuroQoL (EQ-5D-5L): a general quality of life questionnaire, to evaluate health utilities and the corresponding quality adjusted life years (QALYs) [45].Pelvic Floor Disability Index-20 (PFDI-20): to measure symptom distress on disease specific quality of life, focusing on POP, urinary incontinence, and fecal incontinence [46].Pelvic Floor Impact Questionnaire-7 (PFIQ-7): to measure impact on specific quality of life, focusing on POP, urinary incontinence, and fecal incontinence [46].Most Bothersome Symptom questionnaire: to assess the most bothersome urogenital symptoms [47].The Pelvic organ prolapse Incontinence Sexual Questionnaire-IR (PISQ-IR): a condition-specific measure of sexual function in women with pelvic floor dysfunction, including urinary and anal incontinence and pelvic organ prolapse [48].Medical Consumption Questionnaire (iMCQ): for cost effectiveness analysis [49].Productivity Cost Questionnaire (iPCQ) to assess productivity loss [50].Adherence questionnaire: on adherence to treatment, experience using perioperative vaginal cream and influencing factors on compliance. This questionnaire has been developed for this study and is provided as Additional file 1.Adherence diary: a perioperative diary will be kept on the use of vaginal cream, from start till 6 weeks postoperative. Adverse reactions associated with vaginally administered estriol cream (e.g. temporary itch or irritation of the application site) can be reported in the diary as well.Adherence to treatment: Study medication will be delivered at the participant’s home address at two time points; 2 tubes at randomization and 3 tubes at 5 months post-randomization. Participants are asked to return the study medication at 5 months post-randomization and at the end of the study—12 months post-operative. In order to asses adherence to treatment, tubes will be weighted on a scale (Denver Instrument Company, TR-602, digit: 0.01 g) and recorded in Castor EDC.

In case of non-completion of questionnaires, a first reminder will be sent by email after two weeks. If necessary, a second reminder will be sent after 3 weeks. In case of persistent non-completion after 4 weeks, the participant is contacted by telephone by the research nurse.

#### Long-term outcomes

The intention is to evaluate the long-term outcomes of the participants as well (e.g. 3 or 5 years postoperative). When this seems valuable after the 1 year analysis, MEC approval will be obtained in a separate amendment. Permission to approach the participants for this follow-up research is obtained at the time of the informed consent procedure.

### Monitoring and safety

To assure high quality research data and secure patient safety, adequate monitoring will be performed in accordance with the GCP guidelines. Monitoring will be coordinated by the Dutch NVOG Consortium 2.0 and will be executed by a qualified independent monitor. Based on the NVOG Site Monitoring Plan 3.1 of the Dutch NVOG Consortium, remote initiation visits and monitoring visits in each participating center will be performed every year. The independent monitor will have access to the data and source documents of the trial to review the quality of the participating centers. More detailed information can be found in the monitoring plan of the study via www.zorgevaluatienederland.nl/eva. Serious adverse events and any other significant problems will be reported to the medical ethics committee of the Amsterdam Medical Center. A data safety monitoring board will not be installed for this study since perioperative topical estrogens are commonly used in daily practice and use within this study is not perceived to pose an additional risk. Also no interim analysis for efficacy will be performed.

### Insurance

According to national guidelines, a liability insurance and also an insurance that covers injury to participants caused by this study are taken out. These insurances cover injuries up to 4 years after the end of the study.

### Statistical analysis

#### Sample size

The sample size is based on the primary endpoint of subjective cure rate (PGI-I) at 12 months postoperative. A difference in subjective cure of more than 15% is considered clinically relevant. Assuming a subjective cure of 80% in the intervention group and a subjective cure of 65% in the control group; 136 women in each trial arm are needed to assess superiority of the intervention, with a power of 80% and an α of 0.05. With an expected 10% loss to follow up, a number of 150 women will be included in each trial arm (total sample size 300 women).

#### Data analysis

Both an intention-to-treat analysis and per protocol analysis will be performed to evaluate the effect of perioperative estrogen; taking possible confounders in consideration such as study withdrawal and missing data. Analyses will be done using SPSS version 26.0. A *p* value of < 0.05 is considered a threshold for significance. Baseline characteristics will be presented using descriptive statistics, with frequencies (numbers, mean or median with respectively percentages, standard deviation or quartiles).

##### Primary study parameter

The primary outcome, subjective cure (PGI-I), will be reported as frequency with percentage and relative risk with 95% confidence interval together with a *p* value for a chi-squared test. Patients are considered to be cured when they state to be “much better” and “very much better” on a 7 point Likert scale.

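### Relevance and sample size are set as an absolute difference, but the primary result gets a confidence interval for the relative risk alone, and its unadjusted test leaves out baseline values already collected

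*Protocol article*

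**What the plan says.** The Sample size section sets the clinical yardstick: "A difference in subjective cure of more than 15% is considered clinically relevant". The planning rates follow: "Assuming a subjective cure of 80% in the intervention group and a subjective cure of 65% in the control group". Since 80 − 65 = 15, the 15% is meant as percentage points. The section concludes that "136 women in each trial arm are needed to assess superiority of the intervention", "with a power of 80% and an α of 0.05", and adds: "With an expected 10% loss to follow up, a number of 150 women will be included in each trial arm".

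The Primary study parameter section fixes how the result is presented. Subjective cure on the PGI-I "will be reported as frequency with percentage and relative risk with 95% confidence interval together with a" chi-squared p value. The article names no risk difference with an interval.

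Three other sections bear on the choice of model:

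- **Data analysis** says confounders will be considered. Its examples are withdrawal and missing data, which arise after randomisation. It names no baseline covariate.
- **Hospital visits** has POP-Q measured at the visit before study medication starts.
- **Secondary study parameters** compares PFDI-20 at baseline with 12 months, so a baseline PFDI-20 is collected.

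**The concern.** The yardstick is on one scale and the only planned interval is on another. A relative risk corresponds to 15 points only at a given control rate, and the trial will observe a control rate that may differ from 65%. A reader who wants to know how far the data support a gain of 15 points needs the interval for the difference, and the plan does not provide it. The article intends the results to feed a national guideline, so that question will be asked. If the interval is produced only after the data are seen, its method and its reading against 15 points will not have been prespecified.

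The second part concerns efficiency. The trial is planned at 80% power with little margin, and two baseline measures of the condition being treated are collected but have no stated role in the primary analysis.

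**Working it through.** **Inputs.** From Sample size: control rate 0.65, intervention rate 0.80, 136 per arm, power 80%, α 0.05 (sidedness not stated; two-sided reproduces the figure), 150 per arm randomised, 10% loss. Evaluable per arm: 150 × 0.90 = 135.

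**1. The plan's own figure.** With unpooled variance, n = (1.960 + 0.842)² × (0.80×0.20 + 0.65×0.35) / 0.15² = 7.849 × 0.3875 / 0.0225 = 135.2, so 136 per arm, as stated. The pooled formula gives 138, within 2 women. The sample size is reproduced, and it assumes an unadjusted comparison of two proportions.

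**2. Relative risk against absolute difference.**

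| Control cure | RR equal to +15 points | Points gained at RR 1.231 |
|---|---|---|
| 50% | 0.65/0.50 = 1.30 | 11.5 |
| 65% | 0.80/0.65 = 1.23 | 15.0 |
| 75% | 0.90/0.75 = 1.20 | 17.3 |
| 80% | 0.95/0.80 = 1.19 | 18.5 |

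An interval for the relative risk therefore does not translate into an interval for the difference by a fixed rule.

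**3. Smallest significant difference at 135 per arm, with 88/135 (65.2%) cured on control.**

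- 102/135: difference 14/135 = 10.4 points, pooled proportion 190/270 = 0.704, SE = √(0.704 × 0.296 × 2/135) = 0.0556, z = 1.87. Not significant.
- 103/135 (76.3%): difference 15/135 = 11.1 points, pooled proportion 191/270 = 0.707, SE = 0.0554, z = 2.01. Significant.

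For 103 versus 88, the Wald interval for the difference uses SE = √(0.763×0.237/135 + 0.652×0.348/135) = 0.0550. This gives 11.1 ± 10.8, that is 0.3 to 21.9 points.

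The planned output for the same data would be RR = 103/88 = 1.17. Its log SE is √(1/103 − 1/135 + 1/88 − 1/135) = 0.0791, giving a 95% CI of 1.00 to 1.37. The 15-point value does not appear on that scale.

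**4. At the design rates.** SE = √(0.3875/135) = 0.0536. The difference is 15.0 points (95% CI 4.5 to 25.5), beside RR 1.23 (1.06 to 1.43).

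**5. What adjustment could add.** Power with pooled variance is Φ[(0.15√n − 1.960√0.39875)/√0.3875], where 0.39875 = 2 × 0.725 × 0.275. At n = 135 this is Φ[(1.743 − 1.238)/0.622] = Φ(0.81) = 79.1%. If baseline covariates explain a share R² of the outcome variance, the effective n is approximately 135/(1 − R²). The document gives no R², so these values are assumed:

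| R² (assumed) | Effective n per arm | Power |
|---|---|---|
| 0 | 135.0 | 79.1% |
| 0.05 | 142.1 | 81.2% |
| 0.10 | 150.0 | 83.2% |
| 0.15 | 158.8 | 85.3% |

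**The case against.** The strongest reply is that the plan already reports both arm percentages. The point difference follows by subtraction, and anyone with the counts can compute an interval. This stands, so the stronger claim that the result could not be compared with 15 points at all is not supported. What is missing is the planned interval and a statement of how it will be read.

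A reader might also infer that 15 points is a criterion the trial must meet, so that significance at 11 points is a defect of the test. The document does not say this. Sample size calls the difference clinically relevant and uses it to size a superiority trial; it sets no rule that the interval must clear it. Any superiority test with 80% power at 15 points can be significant below 15. Nor would the added interval settle the matter. At about ±10.5 points, showing more than 15 would need an observed difference of about 25.5, and excluding 15 would need one below about 4.5. The interval makes that uncertainty visible but does not remove it.

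A third inference would be that the unadjusted chi-squared test is wrong, or that the centres must be modelled. Neither is supported. The Randomization section says "Women will be randomized in a 1:1 ratio to perioperative treatment with estriol or perioperative treatment with placebo using computer-generated randomly permuted blocks" and names no stratification factor, so the unadjusted test is valid and agrees with the sample size method. Recruitment from "22 participating centers in the Netherlands, i.e. university, teaching and non-teaching hospitals" does not by itself require a centre term in an individually randomised trial. With about 14 women per centre (300/22), adding one is a trade-off that the document does not settle, and it is not proposed here.

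Finally, covariate models are often left to an analysis plan, which is not shown, and the document does not establish that POP-Q stage or PFDI-20 predicts PGI-I success. Both points stand. Adjustment is therefore offered as an improvement on the stated method, and the absence of a model is not counted as an error.

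**Conclusion.** The point holds in a limited form. Relevance and sample size are absolute, the only planned interval is relative, and the interval that would show how the result stands against 15 points is not planned. At 135 evaluable per arm and 65.2% control success, significance begins at 11.1 points with an interval from 0.3 to 21.9. These figures rest on the planned 10% loss and on a control rate near the planned one.

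The sample size and the validity of the test are unaffected. The gain from adjustment is conditional: about 2 to 6 percentage points of power for an assumed R² of 5% to 15%, and almost none if the covariates hardly predict the outcome. This is an inexpensive improvement in reporting and precision.

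**What to change.** - **Effect estimate.** Make the absolute risk difference with 95% CI the primary estimate, keep the relative risk with its CI beside it, and state in one sentence that the difference and its interval will be interpreted against the 15-point relevance value. Make clear that superiority is still judged against zero.
- **Model.** Obtain the risk difference and relative risk by standardisation from a logistic model with arm, baseline POP-Q stage and baseline PFDI-20. Fix in advance how the covariates are coded, how missing baseline values are handled and how the interval is computed. State that the test of the standardised difference is primary and that the unadjusted chi-squared test is supportive, so that it is clear which p value decides.
- **Wording.** In Data analysis, replace the general reference to confounders with these named covariates, and treat withdrawal and missing data separately.

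The cost is a few sentences, settled before unblinding, and a little more analysis work. The sponsor should check that the named software can carry out the standardisation, or name another package. No new data are needed and the sample size does not change.
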